### Study procedures

This study is a pragmatic trial, which implies physicians are allowed to follow local guidelines concerning the treatment of these injuries apart from the intervention investigated. Participating centres are however informed that the preferred surgical technique is a tricortical 3.5 mm diameter screw between 2 and 4 cm of the pilon. If a large reduction clamp is used, the preferred technique is the use of a temporary K-wire as ‘glide path’ [22]. Besides this, participating centres are allowed to choose their own postoperative treatment routine: for example in the use of a cast, non-weight bearing regime and timing of syndesmotic screw removal (within the predefined time window). At 3 months following the index procedure, patients are assessed at the outpatient clinic. Patients are instructed to visit the outpatient clinic sooner in case of any signs of a POWI: warmth, redness, pain, drainage or a fever above 38.5 degrees Celsius. During the visit to the outpatient clinic the patients are seen by their treating physician and the coordinating investigator. The coordinating investigator will document signs of POWI and will determine its presence or any special findings on physical examination. Furthermore patients are requested to fill out several questionnaires (Table 1). At the six and 12 months follow-up, patients are requested to fill out the same questionnaires and the range-of-motion is measured. Follow-up will take place within a window of 2 weeks of the projected follow-up moment.

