### Secondary outcomes

#### Secondary outcome measures of the study are:

Functional outcome with the American Orthopedic Foot and Ankle Hindfoot Score (AOFAS) [24]Pain as measured by a ten-point Visual Analog Scale.Range of motion, both absolute and as a percentage compared with the uninjured side.Postoperative wound infections classified using the criteria as defined by The Centers for Disease Control and Prevention (CDC-criteria) [25]Synostosis or recurrent diastasis (as seen on radiographs made in case of symptoms)Health-related quality of life as measured by the EQ-5D-5 L questionnaire [26].Health care resources utilization (including amongst others; number of visits to the general practitioner and use of home care organizations) as measured by way of a combination of the Dutch/English iMTA Medical Consumption Questionnaire (iMCQ) and iMTA Productivity Cost Questionnaire (iPCQ) (only applicable for the Dutch study population).Costs (economic evaluation including budget impact analysis): the economic evaluation of the RODEO-trial will be performed as a cost-effectiveness (CEA) as well as a cost-utility (CUA) analysis (only applicable for the Dutch study population).

Furthermore general demographics will be assessed such as age, gender, body mass index, co-morbidities, American Society of Anesthesiologists (ASA) classification, substance abuse, level of activity, bone mineral density (when available), fracture characteristics, surgical characteristics, duration of non-weight bearing period and use of physiotherapy.

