### Sample size

We based our sample size calculation on a non-inferiority design. The Olerud-Molander score (OMAS) will serve as primary outcome measure. We have used the results from an earlier study on this subject for our sample size calculation [27]. For the sample size calculation we hypothesized an equal OMAS between the two groups. Using a one-sided significance level (α) of 0.025 and a power (ß) of 90% with a standard deviation (SD) of 19 points (derived from the study mentioned before) and setting our non-inferiority limit at 10 a total of 76 patients are needed in each study arm. Taking a 10% loss to follow-up into account, a total number of 167 subjects will be needed to demonstrate non-inferiority between the two treatment strategies. Furthermore we performed a sample size calculation for a subgroup analysis based on age. We hypothesize that the SD will be lower in these subgroups due to increased homogeneity, therefore we have used an SD of 16 for the sample size calculation of the subgroups. Using a significance level (α) of 0.05 and a power (ß) of 90% 88 patients are needed in each subgroup to prove non-inferiority. Taking 10% loss to follow-up into account a total of 193 patients need to be randomized.

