### Statistical analysis

The primary endpoint will be analysed according to the intention-to-treat and the per-protocol principle, non-inferiority will only be declared if both types of analysis prove non-inferiority. The primary endpoint will be analysed using a one sided test for non-inferiority with an alpha of 0.025. Descriptive methods will be used to assess quality of data, homogeneity of treatment groups and endpoints. Normality of the data will be analysed by visually inspecting the histograms. Secondary outcomes will be analysed using either a t-test or Mann-Whitney U test for continuous data according to the distributing of the data and a Chi Square test for categorical data. Missing data will be handled through multiple imputation with predictive mean matching. All analyses will be performed using the standard statistical software. Separate analyses will be performed on subgroups based on age. A multivariable analysis will be performed to identify predictors of worse functional outcome.

The CEA and CUA will be performed on the intention to treat data, with a time horizon of 12 months and from a societal perspective. The primary economic outcomes are the costs per quality adjusted life year (QALY) and the costs per point functional recovery improvement. Moreover a budget impact analysis (BIA) will be performed with a time horizon of 4 years. The questionnaires estimating the secondary outcome measures ‘resources utilization’ and ‘costs’ will only be used in patients included in the Netherlands due to practical feasibility and to ensure a valid outcome.

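### Histograms decide between t-test and Mann-Whitney for the secondary outcomes, and raw Mann-Whitney and chi-square results neither pool directly over imputations nor bound harm; prespecify effect estimates with 95% CIs

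*Protocol article*

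**What the plan says.** The relevant text is in the Statistical analysis section of the protocol article.

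- On how distribution is judged: "Normality of the data will be analysed by visually inspecting the histograms".
- On continuous secondary outcomes: "Secondary outcomes will be analysed using either a t-test or Mann-Whitney U test for continuous data according to the distributing of the data".
- On categorical ones: "a Chi Square test for categorical data".
- On missing values, in the next sentence and not limited to the primary endpoint: "Missing data will be handled through multiple imputation with predictive mean matching".

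On timing, the Study procedures section says: "At the six and 12 months follow-up, patients are requested to fill out the same questionnaires and the range-of-motion is measured". Together with Table 2, this places the AOFAS, the pain VAS, range of motion and the EQ-5D-5L at 3, 6 and 12 months. Wound infection is marked in Table 2 at 3 months only. Synostosis and recurrent diastasis are secondary outcomes found only on radiographs taken because of symptoms.

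The section names tests for the secondary outcomes. It names no effect measure for them and no model that uses the three visits together.

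**The concern.** Three features of the stated rule work against one another.

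1. **The test is chosen after the outcome is seen.** The t-test compares means. Mann-Whitney U asks whether a value from one arm tends to exceed a value from the other. Choosing between them by eye lets the data decide which treatment contrast is reported. With several imputed data sets it is also unclear which histogram decides.

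2. **Two of the three named tests do not feed multiple imputation directly.** Rubin's rules combine an estimate and its variance from each imputed data set. A raw U or chi-square statistic supplies neither.

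3. **A difference test does not bound harm.** The Discussion says that non-inferiority on the OMAS would be a strong argument for making removal on demand standard care. Readers will then ask how much worse the other outcomes could be, and a p-value above 0.05 does not answer that. The Background discounts a systematic review's result of no significant difference because it rested on one underpowered trial and weak case series. Reporting the secondary outcomes by p-value alone would invite the same criticism.

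**Working it through.** **The plan's own figure.** No stated number depends on this rule. The one nearby figure that can be checked is the primary sample size. Inputs from the Sample size section are SD 19, margin 10, true difference 0, one-sided alpha 0.025 and power 90%.

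n per arm = 2 × (1.960 + 1.282)² × 19² / 10² = 75.9, so 76, as stated. It does not bear on the secondary outcomes.

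**What each named test supplies for pooling.** Rubin's rules need, from each of M imputed data sets, an estimate q and its variance u. The pooled estimate is mean(q), and its variance is mean(u) + (1 + 1/M) × var(q).

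| Test | Output as usually run | Enters Rubin's rules directly? | What would have to be added |
|---|---|---|---|
| t-test | mean difference and SE | yes | nothing |
| Mann-Whitney U | U and p-value | no | P(X>Y) with its variance |
| chi-square | statistic and p-value | no | risk difference or log odds ratio with SE, or the D2 rule for combining chi-square statistics |

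**Can the additions work?** A null simulation used 1,000 replicates, 97 per arm and about 10% of 12-month values missing depending on the 6-month value. Imputation was by predictive mean matching with 10 imputations. SD 19 and 10% loss come from the protocol. The 6-to-12-month correlation of 0.6, the missingness model and the number of imputations are assumptions. Two-sided rejection rates at nominal 5% were:

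- pooled mean difference: 6.0%
- pooled P(X>Y): 6.0%
- chi-square combined by D2: 4.1%
- pooled risk difference: 4.4%

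The Monte Carlo SE is √(0.05 × 0.95 / 1000) = 0.7 points, so all four are near nominal. Pooling is therefore possible once an estimate or combining rule is added. The simulated scores were normal, and the binary outcome was common: a score below 60 with mean 75 and SD 19 has z = (60 − 75)/19 = −0.79, about 21%. The simulation does not cover skewed scores or rare events.

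**What a p-value hides for a complication.** Patients with data per arm: 193 × 0.90 / 2 = 86.9, so 87 (193 and 10% loss from the Sample size section). The documents give no complication rates, so event counts are assumed. With 2/87 = 2.30% in each arm, the chi-square statistic is 0 and p = 1.0. The Wilson 95% limits for 2/87 are 0.63% and 8.00%. The Newcombe half-width is

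√[(2.30 − 0.63)² + (8.00 − 2.30)²] = √(2.79 + 32.5) = 5.9 percentage points.

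The same formula with 1, 4 and 8 events in each arm gives half-widths of 5.2, 7.2 and 9.1 points. The test result is p = 1.0 in every case.

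**The case against.** The strongest reply is that a condensed article commonly leaves effect measures, intervals and pooling rules to the full protocol or analysis plan, so their absence is no fault. That stands. The article does not say that only p-values will be reported, and this point does not rest on that omission. It rests on what the article does fix: test choice by histogram, and difference tests for outcomes on which readers will want bounds.

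Four stronger readings are tempting, and the documents do not support them.

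- **That imputation and the named tests are incompatible.** They are not. The t-test is named first for continuous data and pools directly, and the other two can be pooled once a suitable quantity is added.
- **That each outcome will be tested separately at every visit, with inflated false positives.** The article does not say whether visits are tested separately or which visit is compared. A mixed model reporting a difference at each visit would make the same comparisons, so multiplicity is no argument for the change.
- **That chi-square is invalid here because events will be too few.** No event rates are given, so low expected counts are not established. For assumed risks of 1%, 2%, 3% and 5% in both arms with 87 per arm, exact enumeration gives a true size for nominal 5% uncorrected chi-square of 1.0%, 3.5%, 4.4% and 4.2%. It is never above 5%. The case for a risk difference is that it comes with an interval, not that chi-square misleads on significance.
- **That a longitudinal model should replace every test.** It cannot serve wound infection, marked at one visit, or synostosis and diastasis, which are found only when symptoms prompt a radiograph.

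**Conclusion.** The point holds for the secondary outcomes. The histogram rule leaves the treatment contrast for each continuous outcome open until the data are seen. Its Mann-Whitney branch, and the chi-square test for categorical outcomes, give results that need a further step before they combine over imputations. A non-significant result from any of the named tests would not limit how much worse removal on demand could be.

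The consequence is moderate. The primary OMAS non-inferiority conclusion is untouched, no error-rate inflation is shown, and outcomes sent to the t-test have no pooling problem. The size cannot be put in points for AOFAS, VAS, range of motion or EQ-5D-5L, because the documents give no SDs for them. For a complication, the illustration of roughly 5 to 9 percentage points either side of zero rests on assumed counts of 1 to 8 events in each arm and 87 patients per arm. It is worth changing because a better rule is available at little cost.

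**What to change.** 1. Remove the choice between t-test and Mann-Whitney by histogram. Histograms can stay as a description of the data.
2. For AOFAS, VAS, range of motion and EQ-5D-5L, prespecify the between-arm mean difference with 95% CI. Preferably take it from one linear mixed model per outcome over the 3-, 6- and 12-month visits, with arm, visit and arm-by-visit terms. Use robust or bootstrap standard errors if the data are skewed. Where values are imputed, pool the estimate by Rubin's rules. A simple mean difference pooled in the same way would meet the minimum.
3. For wound infection, synostosis and recurrent diastasis, report the risk difference with a small-sample 95% CI (Newcombe or Miettinen-Nurminen) instead of relying on a chi-square p-value.

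The cost is a few sentences of analysis wording and slightly more modelling. The downside is a model-based estimate in place of a simple test. No new data are needed and the primary analysis does not change.

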### Interventions

Patients will be informed about the study by their treating physician following the procedure in which the syndesmotic screw was placed. After this, patients are contacted by the coordinating investigator to request participation in the study. After obtaining signed informed consent patients will be randomly assigned in a 1:1 allocation ratio to one of the following groups:Control group: Routine removal of the syndesmotic screw(s) 8 – 12 weeks following the index procedureor2)Intervention group: On demand removal of the syndesmotic screw(s)

Patients in the control group will undergo routine removal of the syndesmotic screw 8 – 12 weeks post-operatively (according to the preference of the treating surgeon). Patients will not undergo routine removal in case of 1) a contra-indication for undergoing a second procedure for example due to a (new) medical condition or 2) explicit request of the patient after consultation of their treating surgeon. In the intervention group the screw will only be removed in case of symptomatic implants, defined as: 1) implants causing pain, 2) implants (suspected of) causing restricted range-of-motion 3) explicit request of the patient 4) an infection or 5) other problems related to the screw such as protruding screw-head. The screw will only be removed after a consultation of the treating surgeon (except in patients who wish to no longer participate in the study). In patients in the control group in whom the syndesmotic screw brakes prior to planned removal, the screw will be left in place and only removed in case of symptoms.

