## Discussion

Displayed above is the protocol for an adequately powered study investigating the difference in routine removal versus removal on demand of the syndesmotic screw in ankle injuries. This will be the first RCT able to prove whether a statistically significant and clinically relevant difference exists.

Since this is a pragmatic trial, surgeons are allowed to choose their own postoperative treatment routine. This, combined with the 15 participating centres will result in a variation in for example the use of a cast, the duration of non-weight bearing mobilisation and a minor variation in the timing of the removal of the syndesmotic screw. However, we believe that this situation accurately reflects daily practice, considering that slight variations in post-operative treatment regimens are inevitable.

The inclusion of the University Hospital Helsinki makes this trial international. This greatly improves the external validity of the trial. Not all secondary outcome measures can be used in an international setting. The budget impact analysis and the health care resources utilization for example can only be used for patients in the Netherlands. This is due to practical feasibility but also to ensure a valid outcome. When the same (translated) questionnaire would be used in patients in Finland, results would not be extractable since the costs of healthcare (e.g. a surgical procedure or a visit to the physiotherapist) will not likely be the same as in the Netherlands. However, the participation of a hospital outside of the Netherlands will give us more insight in how to implement the results not just in the Netherlands, but in the rest of Europe as well.

If this trial proves that removal on demand is indeed non-inferior to routine removal of the syndesmotic screw(s) in terms of functional outcome, this will offer a strong argument to adopt this as standard practice of care. It would mean that patients will not have to undergo a secondary procedure, leading to less complications and subsequent lower costs.

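### The 12-month cost horizon can overstate the saving from removal on demand, because later removals fall mainly, though not only, in that arm

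*Protocol article*

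**What the plan says.** The Interventions section fixes when removals happen. For controls: "Patients in the control group will undergo routine removal of the syndesmotic screw 8 – 12 weeks post-operatively". For the other arm: "In the intervention group the screw will only be removed in case of symptomatic implants". The listed triggers include pain, restricted motion, infection and the patient's own request, and no end date is given.

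The same section lets some controls keep the screw. One exception reads: "Patients will not undergo routine removal in case of 1) a contra-indication for undergoing a second procedure". Another is the patient's explicit request. If a control's screw breaks before the planned removal, "the screw will be left in place and only removed in case of symptoms".

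Under Study procedures and in Table 2, the last visit and the last cost questionnaires (i-MCQ and i-PCQ, Dutch patients only) are at 12 months.

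The Statistical analysis section sets the economic horizons: "The CEA and CUA will be performed on the intention to treat data, with a time horizon of 12 months and from a societal perspective". It continues: "Moreover a budget impact analysis (BIA) will be performed with a time horizon of 4 years". The inputs to the budget impact analysis are not described.

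The Discussion gives the economic argument, on condition that non-inferiority is shown: "It would mean that patients will not have to undergo a secondary procedure, leading to less complications and subsequent lower costs".

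**The concern.** One strategy incurs its removal cost early and the other spreads it over an open-ended period, yet both are costed over the same 12 months. The scheduled control operations lie wholly inside that window. An on-demand patient who asks for removal at the 12-month visit, is on a waiting list then, or develops symptoms later is costed as having had no second operation. Some delayed operations are thus counted as avoided.

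The avoided operation is the article's main economic reason for changing practice. A one-directional error in that count bears on the cost claim and, depending on how it is modelled, on the 4-year budget impact. It does not touch the primary non-inferiority comparison on the Olerud-Molander score.

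**Working it through.** The article states no cost, saving or late-removal rate, so there is no figure to reproduce. The check is a count of removal operations per patient.

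**Inputs**
- From the article: scheduled control removal at 8–12 weeks; on-demand removal without an end date; some controls keep the screw; last cost data at 12 months.
- c = share of controls whose screw is out by month 12. Not given; assumed 75–100%.
- p = share of on-demand patients whose screw is out by month 12. Not given; assumed 10–30%.
- q = share of screws still in place at month 12 that are removed in months 12–48, taken as equal in both arms. Not given; assumed 0–20%.

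**Formulas**
- Operations avoided per patient, as seen at 12 months: c − p.
- Later removals: (1 − c)q in controls and (1 − p)q on demand.
- Operations avoided by 48 months: [c + (1 − c)q] − [p + (1 − p)q] = (c − p)(1 − q).
- Relative overstatement, if the 12-month count is read as the lasting saving: (c − p)/[(c − p)(1 − q)] − 1 = 1/(1 − q) − 1.

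With a common q, the relative overstatement does not depend on c or p, provided c > p.

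| q | 1/(1 − q) − 1 |
|---|---|
| 0% | 0% |
| 2% | 2.0% |
| 5% | 5.3% |
| 10% | 11.1% |
| 20% | 25.0% |

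**Worked case, c = 85% and p = 20%**
- At 12 months: 0.85 − 0.20 = 0.650 operations avoided per patient.
- q = 5%: 0.650 × 0.95 = 0.6175.
- q = 10%: 0.650 × 0.90 = 0.585, an overstatement of 0.065 operations per patient.

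**Effect of control patients who keep the screw**
If late removals occurred only on demand, the overstatement at q = 10% would be (1 − 0.20) × 0.10 = 0.080. The controls' own late removals, (1 − 0.85) × 0.10 = 0.015, bring it down to 0.065. The two figures agree only when c = 100%.

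**Direction if q differs between arms**
The 12-month count is too high whenever (1 − p) × q on demand exceeds (1 − c) × q in controls. In the worked case 80% of on-demand patients and 15% of controls still have the screw. The late-removal share in controls would have to be more than 0.80/0.15 = 5.3 times that in the on-demand arm to reverse the direction.

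**The case against.** The 12-month horizon is declared openly and matches the primary endpoint and the end of follow-up. As a statement about the first year, the analysis is correct. The Background also suggests that retained screws seldom cause complaints because they loosen or break, so late removals may be rare. This stands as far as size goes: zero cannot be excluded, and the percentages above illustrate assumed values. They also count operations, whereas the analysis is societal and includes productivity and other care, so they do not measure the error in total cost.

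A reader might go further in three ways that the article does not support.

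- *The cut-off removes cost from one arm only.* The exceptions in the Interventions section contradict this. Controls with a contra-indication, a wish to keep the screw or a broken screw can retain it, and later symptom-driven removal is expressly foreseen for broken screws.
- *The 4-year budget impact is built on 12-month data.* This is an inference. Table 2 shows no collection after month 12, but the article is silent on the model's inputs, which may include outside rates or scenarios. The horizon may also be a budget period and not four years of follow-up per patient.
- *The plan does overstate the saving.* This requires late removals to occur in more than negligible numbers, and no rate is given.

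It can also be said that form items and economic sensitivity analyses are usually left to a full protocol or analysis plan. That is fair, and their absence from the article is not counted here as an error. What remains follows from choices the article does state: the removal schedule, the open-ended on-demand rule and the 12-month CEA/CUA horizon.

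**Conclusion.** The concern holds in limited form. The stated 12-month horizon can overstate the saving from removal on demand, because removals pending at or done after month 12 fall mainly in that arm. The direction is clear provided that more controls than on-demand patients have had the screw out by month 12, that some retained screws are removed later, and that the late-removal share is not many times higher in controls.

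The size cannot be derived from the documents. For an assumed q of 0–20% common to both arms, operations avoided are overstated by 0–25%. The effect on total societal cost is unknown. For the 4-year budget impact, the article supports only a request to state how later removals are handled, not a finding of bias. The functional non-inferiority conclusion is unaffected.

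**What to change.** - **12-month visit.** Record for every patient, in both arms, whether the screw is still in place and whether removal has been requested or scheduled. If the full protocol already collects this, use it.
- **CEA and CUA.** Keep the 12-month horizon for the main analysis. Add a pre-stated sensitivity analysis that costs the pending removals in both arms.
- **Budget impact analysis.** State how removals after month 12 are treated, and do not take retention at 12 months as permanent. Vary the later removal rate over a stated range that includes zero, apply it to retained screws in both arms, and report whether the saving persists.

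The cost is one form item at an existing visit and a little more modelling, with no extra visits or patients. The stated saving may come out somewhat smaller.
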